##### B.10.1. *Fatal/life threatening SUSARs*

The sponsor will inform the REC of the above as soon as possible, but no later than 7 calendar days after he has first knowledge of the minimum criteria for expedited reporting.

##### B.10.2. *Non-fatal and non-life threatening SUSARs*

The sponsor will report all other SUSARs and safety issues to OXREC as soon as possible but no later than 15 calendar days after he has first knowledge of the minimum criteria for expedited reporting.

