### Ethical approval

The trial will be conducted in compliance with the principles of the Declaration of Helsinki (1996), the principles of ICH-GCP and run in accord with EU Clinical Trials Directive and all of the applicable regulatory requirements. The study protocol and other documentation have been approved by the Birmingham East, North and Solihull Research Ethics Committee, 14^th ^of June 2010 (REC reference number: 10/H1206/22) and amendment on 21 November 2011 (Amendment number: AM01). Any subsequent protocol amendments will be submitted to the REC for approval and the other bodies if necessary. We will comply with ICH-GCP Guidelines over the reporting of adverse events, serious adverse events, and suspected serious adverse reactions (SUSARS). In addition we will provide the REC with progress reports as well as a copy of the Final Study Report.

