#### B.2. Definition of serious adverse event

A serious adverse event or serious adverse drug reaction is any untoward medical occurrence at any dose that: results in death, is life-threatening (immediate risk of death), requires inpatient hospitalisation or prolongation of existing hospitalisation, results in persistent or significant disability/incapacity, and/or results in congenital anomaly/birth defect. An important medical event may not be immediately life-threatening and/or result in death or hospitalisation. However, if it is determined that the event may jeopardize the participant and may require intervention to prevent one of the other outcomes listed in the definition above, the important medical event should be reported as serious. Examples of such events are intensive treatment in an accident and emergency department or at home for bronchospasm; blood dyscrasias or convulsions that do not result in hospitalisation; or development of drug dependency or drug abuse. Serious adverse events will be those that occur during the period of medication use or within 7 or more days of ceasing medication use.

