#### B.9. Evaluation of AEs for causality

• Not Related. Onset of the event as relative to administration of the product, is not reasonable; or, another cause itself can explain the occurrence of the event

• Unlikely to be related. Onset of the event as relative to administration of the product is possible but another cause itself can explain the occurrence of the event or there are no reasonable grounds for suspecting that the product could have caused the event.

• Possibly related. Onset of the event as relative to administration of the product is reasonable; however the event could have been due to another, equally likely, cause

• Probably related. Onset of the event as relative to administration of the product is reasonable and is more likely explained by the drug than by any other cause.

• Definitely related. Onset of the event as relative to administration of the product is reasonable and there is no other cause to explain the event; or a re-challenge (if feasible) is positive.

AE is classified as "not related" or "unlikely to be related" in case the patient has stopped using NRT seven days or longer at occurrence of the event.

The pharmacists/clinicians' responsibilities and processes for evaluating AEs

The participant will be encouraged to report AEs to the pharmacist, who will manage these in the normal manner for reported AEs. The pharmacist completes a form called: "Undiagnosed health problem or hospitalisation/death/disability log" in the CRF. In the case of SUSARs or SAEs, the pharmacist will report to the PI or other member of the investigating team within 24 hours of becoming aware of such a possible occurrence. In case the research team becomes aware of the occurrence first, the Principal Investigator will inform the pharmacist and fill in the log in the online CRF. It is pharmacist's responsibility to ensure that both versions of the CRF log (online and paper version) are accurate.

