#### B.10. The CI/PI's responsibilities and processes for evaluating AEs

Each AE reported to the PI will be evaluated for seriousness, causality, expectedness and severity. The responsibility for this will lie with [name], the PI..

Reporting to the sponsor will be required where the AE has a possible causal relationship to the trial intervention, and/or is unexpected. In this case [name] will report the event to the sponsor as soon as being made aware of the event. An initial verbal report can be made but will be followed promptly with a detailed written report on the trial SAE form The copy of the form will be filed in the trial master file.

Timeframes in which the Sponsor will submit expedited reports to the Research Ethics Committee (REC) and to the Medicines and Healthcare Products Regulatory Agency (MHRA)

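### Appendix 1 sends non-fatal SUSARs to an undefined committee, gives the SAE window no end, and has two rules that label late events of unknown cause in opposite ways

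*Protocol article*

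**What the plan says.** All places are in the protocol article.

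- **Approving committee.** Under Ethical approval, the protocol and other documentation "have been approved by the Birmingham East, North and Solihull Research Ethics Committee". No other ethics committee is named in full.
- **Lead-in to the timeframes (Appendix 1, B.10).** The sponsor "will submit expedited reports to the Research Ethics Committee (REC) and to the Medicines and Healthcare Products Regulatory Agency (MHRA".
- **Fatal or life-threatening SUSARs (B.10.1).** "The sponsor will inform the REC of the above as soon as possible, but no later than 7 calendar days".
- **Other SUSARs (B.10.2).** "The sponsor will report all other SUSARs and safety issues to OXREC as soon as possible", with a limit of 15 calendar days.
- **Other safety issues (B.10.3).** A letter goes to the REC.
- **SAE window (B.2).** "Serious adverse events will be those that occur during the period of medication use or within 7 or more days of ceasing medication use".
- **Causality by elapsed time (B.9).** An event is put in the not-related or unlikely category "in case the patient has stopped using NRT seven days or longer at occurrence of the event".
- **Causality by assessment (B.8).** The pharmacist or investigator must assess causality for all adverse events, serious or not. If the investigator cannot determine it, the event is treated as related when it is reported.
- **Trigger for reporting to the sponsor (B.10).** An event is reported if it is possibly caused by the trial intervention, or is unexpected, or both.

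**The concern.** These are operating instructions for pharmacists, the investigator and the sponsor. Three of them cannot be followed as written without a guess.

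First, someone applying B.10.2 literally sends reports to a body that the article does not identify. The same clause also covers safety issues, while B.10.3 sends other safety issues to the REC, so one kind of report has two stated destinations.

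Second, the B.2 window can be read as ending at day 7 after stopping or as never ending. The set of events counted as SAEs then depends on the reading.

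Third, B.8 and B.9 give different answers for the same late event. That label matters beyond the table of adverse events. B.3 and B.4 define SSARs and SUSARs as adverse reactions, so an event ruled unrelated leaves the expedited route, and the first limb of B.10's test for telling the sponsor also depends on causality.

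**Working it through.** The plan gives no figure to reproduce, and no sample size, power or event count enters. The check is to set the clauses side by side.

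**1. Recipients**

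| Clause | Events | Recipient named | Sponsor's limit |
|---|---|---|---|
| B.10 lead-in | expedited reports | REC and MHRA | set in the clauses below it |
| B.10.1 | fatal or life-threatening SUSARs | the REC | 7 calendar days |
| B.10.2 | all other SUSARs, and safety issues | OXREC | 15 calendar days |
| B.10.3 | other safety issues | the REC | none stated (the 30 days there is for the committee's acknowledgement) |

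One row of four names OXREC. The name does not abbreviate that of the approving committee, and it occurs only there. B.10.2 and B.10.3 overlap on safety issues and name different recipients.

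**2. The SAE window, counting days from the last NRT use**

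- Read with weight on the word within, B.2 covers time on NRT and up to day 7.
- Read with weight on the words or more, it covers time on NRT and every later day, with no end.

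Both readings use words that are in the sentence, and nothing else in Appendix 1 chooses between them.

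**3. Causality**

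The B.9 rule starts at day 7 after stopping. Events on NRT, or on days 0 to 6 after it, are untouched. Take an event on day 8 whose cause the investigator cannot determine:

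| | Under B.8 (unknown counts as related) | Under B.9 (elapsed time) |
|---|---|---|
| Label | related | not related or unlikely |
| Serious and unexpected | meets the SUSAR definition in B.4; expedited | not a reaction, so not a SUSAR; still goes to the sponsor under B.10 because it is unexpected |
| Expected | goes to the sponsor under B.10 as possibly causal | meets neither limb of B.10, so may not reach the sponsor |

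The labels are opposite in every case. The practical difference is largest for two groups: unexpected serious events lose the expedited route, and expected events lose the B.10 trigger.

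**The case against.** Much can be said for the plan, and part of it stands.

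- **The regulator.** A reader might infer that the MHRA has been left without a deadline, because B.10.1 to B.10.3 do not name it. The documents do not support that. The 7-day and 15-day limits stand under a lead-in that names both the REC and the MHRA, and Ethical approval commits the trial to ICH-GCP and the applicable regulatory requirements. Repeating the MHRA in the clauses is a matter of clarity.
- **SAEs later judged unrelated.** A reader might see a contradiction in counting an event under B.2 and then calling it unrelated under B.9. There is none. Seriousness and causality are separate, and B.10 has the PI evaluate them separately. The conflict is between B.9 and B.8.
- **Central review.** B.5 and B.10 give the investigator and the PI the decision on seriousness and causality, so counts do not rest on each pharmacist alone. That is fair, but central review uses the same open window and sees only what is passed on.
- **B.8 is narrow.** Its default applies only where causality is unknown, and it could be argued that B.9 supplies the missing answer. But then elapsed time replaces the assessment that B.8 requires for every event, and the text does not say which clause prevails.
- **Safety nets.** Unexpected events reach the sponsor under B.10 whatever their label. B.5 can also be read as requiring every SAE to be notified to the sponsor, the NHS R&D office and the REC. On that reading a late, expected SAE is still reported, but B.5 and B.10 then set different triggers.
- **Few events.** Withdrawal criteria expects no SAEs or SUSARs due to the medication. This limits the likely number of events affected; it does not make the clauses agree.

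**Conclusion.** The point holds in three parts: an undefined recipient in B.10.2, an SAE window in B.2 with no usable end, and a time-based causality rule in B.9 that conflicts with B.8.

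Its reach is every SUSAR that is neither fatal nor life-threatening, every SAE whose inclusion turns on where the B.2 window ends, and every event of unknown cause from day 7 after NRT stops. The documents give no expected count for any of these groups, so the effect cannot be put as a number. It is confined to safety reporting.

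Two further inferences go too far. One is that the approving committee would miss most SUSARs: no split between fatal and non-fatal SUSARs is given, and the article does not say what OXREC is. The other is to attach a fixed number of weeks to the period after day 7. That needs a date on which NRT stops, and the plan fixes none: Initial patch dose allows for treatment of nine months and Trial Medication for up to a year, so the period varies by participant and may be nil within follow-up.

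The conclusion assumes only that the article's wording is what sites and the sponsor would follow.

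**What to change.** 1. In B.10.1 to B.10.3, name the approving REC as recipient throughout. If OXREC is meant as an additional recipient, define it and say so. Give safety issues one destination.
2. In the same clauses, repeat that the timeframes also apply to the MHRA, as the lead-in indicates.
3. In B.2, state one closed SAE window after the end of medication use.
4. Reconcile B.9 with B.8 so that causality comes from an assessment of each event. Elapsed time since the last NRT use can be recorded as information for that assessment.

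The cost is a few sentences in Appendix 1, an amendment submitted to the REC as Ethical approval already provides, and a note to the participating pharmacists. No design element, sample size, treatment or efficacy analysis changes.

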##### B.10.3. *Reporting other safety issues*

A letter entitled Safety Report will be sent to the REC where other safety issues also qualify for expedited reporting by the sponsor. The Co-ordinator of the main REC will acknowledge receipt of safety reports within 30 days.
